## Abstract

**Background:**

Borderline personality disorder (BPD) is associated with an intensive use of mental health services, even in the absence of a full diagnosis. Early symptom detection and intervention may help alleviate adverse long-term outcomes. Iconic Therapy is an innovative manual-driven psychotherapy that treats BPD symptoms in a specific and intensive manner. Preliminary results are promising and the indication is that Iconic Therapy may be effective in reducing BPD symptoms. The aim of this study is to assess how effective Iconic Therapy is compared to Structured Support Therapy in a real clinical setting.

**Methods/Design:**

Our study will be a controlled 12-month pragmatic, two-armed RCT. A total of 72 young people (15 to 25 years old) with suicidal ideation/self-injuring behaviour and BPD traits and symptoms will participate in the study. The subjects will be randomised into two groups: Iconic Therapy or Structured Support Therapy. The participants will be assigned to either group on a 1:1 basis. Both the Iconic Therapy and the Structured Support Therapy programmes consist of 11 weekly sessions delivered by two trained psychologists in a group format of between 8 to 12 outpatients. The primary outcome will be measured by the change in symptom severity. Secondary outcomes include changes in suicidal ideation/ behaviour, non-suicidal self-injury, maladjustment to daily life and cost-effective analysis. The primary outcome will be a decrease in the severity of BPD symptoms as assessed by the Borderline Symptom List (BSL-23). For the clinical evaluation, three study assessments will take place: at baseline, after treatment and at 12-month follow-up. We hypothesise that patients attending the Iconic Therapy group will show a significantly higher reduction in symptoms than those in the Structured Support Therapy group. Data will be analysed using generalised estimating equation (GEE) models.

**Discussion:**

By responding to the need for briefer and more comprehensive therapies for BPD, we foresee that Iconic Therapy may provide an alternative treatment whose specific therapeutic principles, visually represented on icons, will overcome classical Structured Support Therapy at reducing BPD symptoms.

**Trial registration:**

NCT03011190

## Background

The characteristics of Borderline Personality Disorder (BPD) are dysregulation of emotional, behavioural and interpersonal relations [1]. BPD is very prevalent among teens and young adults, but diagnosis is often delayed and early treatment rarely offered [2]. Studies show that, with a diagnosis rate ranging from 0.5 to 31.2% among this young population [3], BPD is a disorder with a high social and economic impact, of which the most severe consequence is suicide.

Emotional dysregulation, or mood instability, has been defined as rapid oscillations of an intense affect with a difficulty in regulating said oscillations or their behavioural consequences [4] and is a key factor in the development and maintenance of BPD [5]. Associated with emotional dysregulation, suicidal ideation and behaviour is another psychiatric problem that usually occurs [6, 7]. Severe cases of emotional dysregulation approaching the criteria for BPD diagnosis have a global suicide rate of 8% [8]. An important risk factor for suicide is self-injury behaviour [9], which is considered as an intentional, self-directional act to harm oneself [10]. It is estimated that around 50% of suicidal adolescents have had previous self-injury behaviour [11]. One of the reasons adolescents show affinity to self-injury seems to be their lack of ability to regulate emotions [12, 13]. In fact, self-injury is considered a maladaptive coping mechanism rather than an intentional act to die [14], despite the fact that suicide may result in death for the habitual self-injurer [15]. Nevertheless, personality traits are more malleable and sensitive to change during adolescence [16, 17] and for that reason, early detection and intervention of self-injury behaviour is a unique opportunity to prevent an aggravation of emotional instability, BPD diagnosis and suicidal acts.

To date, the majority of studies have recommended psychotherapy as the main treatment for people with BPD [18], but in clinical practice, pharmacotherapy is the primary treatment, even though the benefits are unclear [19, 20]. Several manualised psychotherapies for BPD have proven their beneficial effects to date [21]. One recent meta-analysis [22] suggests that Dialectical Behaviour Therapy (DBT) [23] and psychodynamic psychotherapies (e.g., Mentalization-Based Therapy (MBT) [24] and Transference-Focused Therapy (TFT) [25]) are more effective than non-specialised psychotherapies or treatment as usual (TAU). Other psychotherapies, such as Schema-Focused Cognitive Therapy (SFT) [26] and STEPPS (Systems Training for Emotional Predictability and Problem Solving) [27], have also shown effectiveness in the treatment of BPD. Regarding evidence-based treatments for self-injury behaviour, very few studies exist to date [28–30].

From a general scientific setting, recommendations to develop innovative therapies by combining and adapting current treatments have been made [2, 31–36]. Iconic Therapy is a comprehensive psychological intervention that integrates existing therapeutic principles proven to be effective in educating people who have difficulty regulating their emotions. What makes Iconic Therapy different from many other approaches is the use of images to help those affected by BPD understand the origins and mechanisms of perpetuation of their emotional instability, feel validated and acquire the necessary attitudes and skills for daily life during a 12-week intensive programme. These images (a total of 35) include pictures, drawings and coloured geometric figures of neutral emotional valence (such as a table, a sailboat or a tower of books) that symbolically represent therapeutic principles (e.g., acceptance, resilience or empathy). The group of participants visualise from 2 to 5 icons per session on a big screen as the therapist explains their therapeutic symbolism, which seemingly eases a better understanding and more rapid evocation of therapeutic clues in crisis moments. Iconic Therapy was created in 2004 by the psychologist [name] and first trialled in a personality disorder unit at a psychiatric hospital in Málaga. It has also been used in other locations across Spain, supported by a text book (Iconic Therapy) [37]. Guidelines for Iconic Therapy have been prepared and are currently pending publication. It contains examples and a number of therapists’ considerations.

Iconic Therapy is a two-part programme composed of a) an intensive 12-week programme and b) an additional 1- to 2-year programme. The intensive programme duration is typically 10–12 weeks, but can vary among users depending on the group’s particular motivation and participation. Therapy is administered to patients as a group and includes weekly sessions led by a therapist and co-therapist in a classroom setting similar to a psychoeducative seminar or workshop. Each group consists of 8 to 12 participants on an outpatient basis. At the end of each and every group session, the Iconic Therapy materials are handed out so participants can keep them as a resource during difficult periods. An additional number of 6 to 8 one-on-one sessions with the therapist are inserted every 2 sessions from the onset of the programme. During the second phase of the Iconic Therapy programme, an additional year of treatment will be offered. It will consist of 3–6 face-to-face sessions with the therapist that become less frequent over the duration of the course. Individual sessions from both parts of the Iconic Therapy programme are a key element; as during this time, patients are taught to select for themselves the best icon for every situation, thus learning new behavioural skills in the relevant context. Iconic Therapy is an intensive treatment to be delivered alone or as a complement to their usual treatment, depending on the history and severity of the symptoms.

When considering the effectiveness of Iconic Therapy on BPD symptoms, preliminary studies have shown good clinical results, including a decrease in functional impairments [38] and assertive behaviour amelioration [37, 38]. The first preliminary study [38] took place on 7 BPD diagnosed patients in the context of a psychiatric hospital ward and showed a significant improvement in emotional dysregulation, relationship instability and impulsivity as well as increased assertive behaviour (familiar, academic and social) 2 years after receiving Iconic Therapy. The second study [39] followed 4 outpatient adolescents attending a public mental health service and having 2 or more BPD DSM-IV-TR criteria. It showed a non-significant improvement in emotional dysregulation, relationship instability and impulsivity as well as equally non-significant assertive behaviour achievements after treatment, which may be explained by the small sample size. Still remarkable is the high adherence and null dropout rate, suggesting good treatment acceptance by patients. Despite the promising results, it is important not to overlook the fact that both of these preliminary studies lack a control group, which importantly limits their relevance.

This clinical trial is aimed at overcoming this limitation by comparing two groups: Iconic Therapy and Structured Support Therapy. It is hypothesised that participants receiving Iconic Therapy will demonstrate greater improvement in severity of BPD symptoms after treatment and at 12-month follow-up compared to those receiving Structured Support Therapy. As a secondary hypothesis, impairment in adaptive functioning (suicidal ideation, suicidal behaviour, maladjustment to daily life and use of services) is expected to improve in parallel.

## Methods

### Study design

The study is planned as a 12-month pragmatic, two-armed parallel randomised controlled trial (RCT). It will randomise 72 young subjects (aged between 15 and 25) with suicidal ideation and/or self-injuring behaviour and borderline personality traits. Participants will be randomly assigned to one of two groups, Iconic Therapy or Structured Support Therapy, on a 1:1 basis to form 4 groups of 18 patients. Two of these groups will be included in the Iconic Therapy group and the other two in the Structured Support Therapy group. A total of 8 volunteer psychologists will administer the therapies formed into 4 pairs of therapists and co-therapists. The volunteer psychologists are required to have obtained a Master’s Degree in Psychology and have previous experience with patients. It is inherently not possible to blind psychologists delivering the Iconic Therapy intervention, since they have been specifically trained for 10 months. The goal of the psychologists conducting the control group is to obtain good clinical results. They will achieve this through therapeutic intervention.

Primary and secondary outcome measures will be assessed at baseline, after treatment (10–12 weekly sessions) and at 12-month follow-up (15 months after the baseline). Study variables and assessment times are shown in Table 1.

**Table 1 Tab1:** Study variables and assessment time

Instrument	Assessment area	Time of assessment
Primary outcomes		
BSL-23^a^	BPD symptoms severity	Baseline After treatment At 12 months
Secondary outcomes		
C-SSRS^b^	Suicidal ideation or behaviour	Baseline After treatment At 12 months
DSM-V criteria^c^	Non-suicidal self-injury diagnosis	Baseline After treatment At 12 months
CSRI^d^	Economic evaluation	Baseline At 12 months
Subsidiary measures		
IG^e^	Daily life adjustment	Baseline After treatment At 12 months
CEQ^f^	Credibility/expectancy questionnaire	After treatment At 12 months
Ad hoc scales^g^	Perceived subjective global improvement *(self-reported)*	After treatment At 12 months
Ad hoc scales^h^	Perceived global improvement *(family/friends reported)*	After treatment At 12 months

Notes. BSL-23^a^ (Borderline Symptom List- short form); C-SSRS^b^ (Columbia Suicide History Form); DSM-V criteria^c^ (Non-suicidal self-injure diagnosis according to the Diagnosis and Statistical Manual of Mental Disorders, DSM- V); CSRI^d^ (Client Service Receipt Inventory); IG^e^ (maladjustment scale)**;** CEQ^f^ (credibility/expectancy questionnaire); Ad hoc scales^g^ (Perceived subjective global improvement); Ad hoc scales^h^ (Family and friends’ perceived global improvement)

For ethical reasons, participants of the comparison group may attend Iconic Therapy once the study is completed. The study flowchart is shown in Fig. 1*.*

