#### Randomisation

Once grouped by age, the principal investigator will randomise patients into either the Iconic Therapy group or Structured Support Therapy group on a 1:1 basis.

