#### Data analyses

Patients will be included in intent-to-treat analyses. Participants’ demographic characteristics will be summarised using descriptive statistics, and the comparability of the treatment groups will be examined using *χ*^2^ tests for categorical variables and *t* tests for continuous variables.

Data analyses of the primary and secondary outcomes will be conducted using generalised estimating equation (GEE) models. Essentially, GEE models extend generalised linear models (GLMs) to allow analysis of repeated measurements or other correlated observations. The response can be scale, counts, binary or events-in-trials. In addition, GEE models can also deal with data that have missing values as long as the missing value is completely random. Parameter estimation can still yield robust results [51].

In these GEE models, treatment conditions (experimental vs. control) will be included as the between-subjects factor and time (baseline, after treatment and at 12 month follow-up) as the repeated measure. Main effects and interaction between treatment and time will be examined. When the interaction effect is statistically significant, simple main effects analyses will be conducted.

IBM SPSS (version 22.0 for Windows) will be used for the statistical data analyses. Statistical significance will be defined as *p* < .05. Bonferroni correction will be applied for post hoc multiple comparisons.

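### Therapy-group and therapist-pair clustering enters neither the sample size nor the GEE, and four groups of 18 contradicts the stated 8 to 12 per group

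*Protocol article*

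**What the plan says.** **Delivery.** Study design forms the arms "on a 1:1 basis to form 4 groups of 18 patients". It continues: "Two of these groups will be included in the Iconic Therapy group and the other two in the Structured Support Therapy group". On staffing it says: "A total of 8 volunteer psychologists will administer the therapies formed into 4 pairs of therapists and co-therapists". With four pairs and four groups, the plain reading is one pair per group. Both programmes are delivered as group sessions (Iconic therapy group; Structured support therapy group).

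**Group size elsewhere.** The abstract (Methods/Design) describes both trial programmes as "delivered by two trained psychologists in a group format of between 8 to 12 outpatients". The Background, describing Iconic Therapy in general, says "Each group consists of 8 to 12 participants on an outpatient basis".

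**Sample size.** The inputs are an effect size labelled Cohen's d of 0.20, power 0.80, a one-tailed test at 95% confidence, 26 per arm (52 in total), and recruitment of at least 72 to cover dropout. There is no ICC and no design effect.

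**Analysis.** In the GEE, "treatment conditions (experimental vs. control) will be included as the between-subjects factor and time" is the repeated measure; the treatment-by-time interaction is also examined. The section remarks in general terms that GEE can accommodate correlated observations other than repeated measurements, but does not apply this to therapy group or therapist. The six limitations in the Discussion do not include clustering.

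**The concern.** Patients are randomised individually, but each is then treated in a group with a shared therapist pair, shared sessions and shared role-play or debate. The Background itself says that programme length can vary with a group's motivation and participation, so it recognises an influence at group level. Where such influences make outcomes alike within a group, two patients in one group carry less information than two independent patients. A model that knows only patient and arm would then give confidence intervals that are too narrow and too many false positives. With two groups per arm, an apparent treatment effect could also come largely from one strong or weak therapist pair.

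The group-size conflict bears on the same question. The number of groups sets the degrees of freedom for any analysis that respects grouping, and the article supports two different answers.

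**Working it through.** **1. The plan's own figure.** With d = 0.20, one-sided 5% and power 0.80, the two-sample formula n = 2(z₀.₉₅ + z₀.₈₀)²/d² gives 2(1.645 + 0.842)²/0.04, or 310 per arm after rounding up, not 26. That is a separate problem. It matters here only because power has to be worked from some effect size. I use the d that 26 per arm would detect on the plan's one-sided basis: (1.645 + 0.842)·√(2/26) = 0.69. The article does not state this value.

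**2. Capacity (no assumptions).**
- As in Study design: 4 × 18 = 72.
- As in the abstract: 4 × 12 = 48 at most, below both 52 and 72.
- 72 patients at 8 to 12 per group: 72/12 = 6 to 72/8 = 9 groups.
- The 52 evaluable patients in four groups: 52/4 = 13 each, above 12.

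**3. Effect of ignoring the group.** Inputs: m = 13 evaluable per group (52/4) and an ICC ρ **assumed** at 0.02, 0.05 and 0.10.
- Design effect: DE = 1 + (m − 1)ρ
- Actual one-sided error: 1 − Φ(1.645/√DE)
- Actual two-sided error: 2[1 − Φ(1.96/√DE)]
- Effective n per arm: 26/DE

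| Assumed ρ | DE | True SE ÷ naive SE | One-sided error | Two-sided error | Effective n per arm |
|---|---|---|---|---|---|
| 0.02 | 1 + 12 × 0.02 = 1.24 | 1.11 | 7.0% | 7.8% | 21.0 |
| 0.05 | 1 + 12 × 0.05 = 1.60 | 1.26 | 9.7% | 12.1% | 16.2 |
| 0.10 | 1 + 12 × 0.10 = 2.20 | 1.48 | 13.4% | 18.6% | 11.8 |

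Both sidednesses are shown because Sample size is one-tailed, while Data analyses sets p < .05 without saying which. A simulation of a patient-level t test with two groups of 13 per arm gave 9.8% and 13.6% one-sided, and 12.3% and 18.9% two-sided, at ρ = 0.05 and 0.10. This agrees with the formulas.

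With all 18 patients retained per group, DE is 1.34, 1.85 and 2.70. The error is 7.8%, 11.3% and 15.8% one-sided, or 9.0%, 15.0% and 23.3% two-sided.

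**4. What four groups can support.** Comparing two group means per arm leaves 4 − 2 = 2 degrees of freedom. At d = 0.69 with 26 per arm, the one-sided power of that test is about 0.50 at ρ = 0, and 0.44, 0.38 and 0.31 at the three assumed values. Most of the shortfall from 0.80 therefore comes from having four groups; the ICC takes a further share.

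**5. Whether a random group effect alone repairs this.** With four groups of 13, the ANOVA estimate of the between-group variance is zero or negative with probability P(F₂,₄₈ < x), where x = (1 − ρ)/(1 − ρ + 13ρ). For 2 numerator degrees of freedom this equals 1 − (1 + 2x/48)⁻²⁴.
- ρ = 0.02: x = 0.98/1.24 = 0.790, probability 54%
- ρ = 0.05: x = 0.95/1.60 = 0.594, probability 44%
- ρ = 0.10: x = 0.90/2.20 = 0.409, probability 33%

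In those trials, a mixed model with a non-negative variance constraint tends to fall back to the patient-level analysis. A GEE clustered on therapy group would have four clusters, too few for a dependable robust standard error.

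**The case against.** **The size is assumed.** No ICC is given, and at 0.02 the inflation is modest. Some of the care is not specific to a group: patients in both arms may see the principal investigator individually, therapists in both arms are supervised, and usual treatment continues. All of this stands. It makes the standard-error statement conditional on a positive ICC and the figures a range.

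**Analysis detail may sit in an analysis plan that is not shown.** This does not clear the point. The article itself fixes the model terms, the sample-size inputs and the number of groups, and grouping is absent from the first two.

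**The 8 to 12 might be attendance after dropout, or the programme in general.** At the 24% to 52% dropout quoted in Sample size, 18 shrinks to between 18 × 0.76 = 13.7 and 18 × 0.48 = 8.6. The article does not offer that explanation, and its own 52 evaluable patients are still 13 per group. The Background sentence does describe the general programme, so it is the weaker support. The abstract describes this trial and both arms.

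**Keeping 8 to 12 might seem to cure the clustering by creating more groups.** A reader might infer this, but Study design provides four therapist pairs. Six to nine groups run by those four pairs add groups without adding therapist-level replication.

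**Grouping by age.** Randomisation says "Once grouped by age, the principal investigator will randomise patients". If therapy groups follow age, their members would be more alike. The article does not say that they do, so I put no weight on it.

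**Conclusion.** Two conclusions hold.

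1. **The group-size contradiction is certain.** Four groups of 18 and 8 to 12 per group cannot both describe this trial.
2. **Clustering by therapy group and therapist pair is built into delivery and absent from both the sample size and the stated model.** For any positive ICC the planned standard errors are too small. Over assumed ICCs of 0.02 to 0.10 with 13 evaluable per group, a nominal 5% test runs at 7.0% to 13.4% one-sided or 7.8% to 18.6% two-sided, and 26 patients per arm are worth about 21 down to 12.

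A reader might infer that the standard errors are known to be too small, or that the larger two-sided figures are the size of the problem. The article supports neither: it states no ICC, and it sizes the trial one-tailed. Nor does it describe the groups as closed; the argument needs only that patients share a group and a therapist pair. The power figures rest on d = 0.69, derived here from 26 per arm, and not on the stated 0.20.

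**What to change.** - **Reconcile** the number of groups, their size and the number of therapist pairs across the abstract, Background and Study design, and say whether each pair runs one group.
- **Put therapy group/therapist pair into the primary analysis**, with degrees of freedom fixed in advance by the number of groups (2 if there are four), and keep that term when its variance estimate is zero. A random effect that may drop out is not enough with two groups per arm.
- **Restate the sample-size justification** with a design effect over a stated ICC range, using the same sidedness as the analysis.
- **If only two groups per arm are run**, show results by group and state that the treatment effect cannot be fully separated from the four therapist pairs. More groups under the same four pairs do not remove that limit; more pairs would be needed.

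**Cost.** The first three items and the reporting statement are changes of wording and calculation. The price is wider confidence intervals and a less favourable stated power. Adding therapist pairs, if chosen, would cost recruitment, training and supervision beyond the eight psychologists named.

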**Fig. 1 Fig1:**
[figure not shown]
Study flowchart and chronogram. TAU: Treatment as usual

### Study aims

The aim of the study is to investigate, by comparison with Structured Support Therapy, how effective Iconic Therapy is in improving participants’ BPD symptoms. The primary outcome measure is a change of symptoms measured through the use of the Borderline Symptom List (BSL-23) post-treatment. Our hypothesis is that patients undergoing Iconic Therapy will show a greater reduction in the severity of their symptoms after receiving the intensive part of the therapy than those undergoing Structured Support Therapy. As a secondary outcome, we hypothesise that these differences will continue to be verifiable at the 12-month follow-up. Other secondary measures are suicidal ideation, suicidal behaviour, maladjustment to daily life and use of services as a consequence of BPD symptoms. We will also evaluate satisfaction with the treatment and perceived subjective global improvement beyond the symptoms.

